### Participating centers

Four centers will enrol patients. Three of these hospitals are Dutch and one University hospital in California is willing to participate. The three Dutch hospitals will consist of 1 regional teaching hospital and two University hospitals. One of the university hospitals, the Academic Medical Center has already started patient recruitment and has included 125 patients in a 15-month period. The other Dutch University hospital, the University Medical Center Utrecht, will start recruiting patients in the summer of 2011 and is also expected to recruit 8-9 patients a month in average. The University hospital in California expects to recruit 50 patients in a one year period. In the regional teaching hospital, the Antonius Hospital in Nieuwegein, approximately 100-150 patients with a wrist, ankle or calcaneus fractures are operated upon yearly. Because this hospital has different locations, for logistic reasons it is not possible to recruit al these patients. It is expected that 75% of these patients will participate in this trial.

### Study outline

#### Recruitment

Patients will be recruited if they are eligible for operative treatment of their intra-articular fracture of the wrist, ankle or calcaneus. This can be at the Emergency Department (ED), the outpatient clinic or the inpatient clinical wards of orthopaedic or trauma surgery. After patients are counselled and informed consent is obtained, they can be included in the study.

#### Intra-operative 3D-scan

For this study the BV Pulsera with 3D-RX (3 Dimensional Rotational X-ray) is used. The BV Pulsera (Philips Healthcare, Best, the Netherlands) consists of a mobile C-arm unit modified to provide a motorized rotational movement and is combined with a Philips 3D-RA workstation. A series of 251 projection images is acquired over a period of 30 seconds during a 200° rotation of the C-arm. The projection images are used to reconstruct a 3D data set. Both volume rendering and slice images are available. The images can be enhanced by colouring the metal present in the joint (Titanview). The radiation exposure of each image in the scanning run is dynamically adjusted to provide the best combination of low dose and optimal image quality. The device is continuously available for the duration of this trial.

#### Radiation dose

Patients with a fractured wrist, ankle, or calcaneus will receive an expected maximum of two 3D-RX-scans, during surgery and two X-rays postoperatively. The maximum equivalent dosage of a 3D-RX-scan of the extremities is 17 μSv. Therefore the additional dosage during the OR of two exams is in the order of 34 μSv. Together with the X-rays performed postoperatively, the radiation dose will approximate 50 μSv. The effective dose of the postoperative CT-exam (120 kV, 150 mAs) will not exceed 0,2 mSv. The total dosage for all radiographic exams performed as part of this trial will therefore be less than 0,25 mSv. A similar effective dose is included in category IIa (0,1-1 mSv) of the ICRP (report ICRP62), which is qualified as a "minor" risk.

### Data collection

Pre-operatively baseline data of the patient and fracture type are collected. Intra-operatively the surgeon will be asked to evaluate the operated joint according to the scoring protocol for anatomical reduction and fixation, which is developed in the AMC. If the 3D-scan is available to the surgeon (s)he will evaluate the 3D-scan intra-operatively according to the scoring protocol mentioned above.

During the follow-up visits at 6 and 12 weeks and 1, 2 and 5 years postoperatively the range of motion, functional outcome and strength of the operated joint will be recorded and compared to the contralateral joint. For wrist fractures the 'Patient rated Wrist Evaluation' (PRWE) score will be used, for ankle and calcaneus fractures the 'Foot and Ankle Outcome Score' (FAOS) will be assessed. Quality of life will be determined by the SF-36. These are validated outcome scores. In addition a questionnaire pertaining questions on work-related items and the patients indirect costs of production loss will be assessed.

All intra-operative images (both 2D-fluoroscopy and 3D-scans) and postoperative CT-scans will be evaluated by 3 independent experts in blinded fashion and random order according to a standard scoring protocol. These experts will consist of 2 trauma/orthopedic surgeons and a radiologist. Data collected by the physicians will be entered in a secured Internet module which is specially designed for the EF3X-trial. Patients will be given the choice to receive digital or paper questionnaires. Collection of data and questionnaires will be safeguarded by the trial coordinator.

### Data monitoring

Because of the size of the trial it was considered important to ensure independent review. Therefore a Data Monitoring Committee (DMC) is set up to ensure the safety of the study participants, provide independent review of safety, ensure the integrity of the study conduct and results and review of the formal interim analysis.

### Data analysis

All analyses will be performed in accordance with the intention to treat principle.

The primary outcome, the quality of fracture reduction as well as the quality of fixation will be classified as optimal or suboptimal. This dichotomous outcome, will be described as a percentage in both groups. Differences between study groups will be analysed by means of a Chi-square test. A p-value < 0.05 will be taken as the threshold for statistical significance.

The scores of the functional outcomes determined by joint specific questionnaires at 1 year postoperative will be expressed as means and standard deviations (SD) in case of a normal distribution. Non-normally distributed outcomes will be expressed as medians and interquartile ranges. Normality of continuous data will be tested with the Shapiro-Wilk and Kolmogorov-Smirnov test and by inspecting the frequency distributions (histograms). The homogeneity of variances will be tested using the Levene's test. The functional outcomes will be assessed using the Student's T-test (parametric data) or the Mann-Whitney *U*-test (non-parametric data). Differences will be considered statistically significant when P-values are < 0.05.

The diagnostic accuracy of a suboptimal quality of fracture reduction and/or fixation will be determined for reduction and fixation for the wrist, ankle and calcaneus separately. Sensitivity, specificity, positive and negative predictive values for both 2D-fluoroscopy and the 3D-RX-scan will be calculated with the corresponding 95% confidence intervals for the classification of an optimal or suboptimal result as described above. This will be determined for both 2D-fluoroscopy and the 3D-RX-scan with the postoperative CT-scan as reference standard.

The number of patients in which corrections were performed intra-operatively after 2D-fluoroscopy or the 3D-RX-scan will be described as percentages. Differences between study groups will be analysed by means of a Chi-square test. The same analysis will be done for the number of patients with a revision operation or complication within 30 days. The length of hospital stay will be expressed as medians and interquartile ranges, and differences between groups will be analysed using a Mann-Whitney U test. The quality of life measured by the SF-36 will be expressed as means and standard deviations (SD) after testing for normal distribution and compared between groups using an unpaired Student t-test. For all secondary parameters a p-value < 0.05 will be taken as the threshold for statistical significance.

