### Choice for the study design

With this study we aim to address multiple issues regarding the intra-operative use of 3D-imaging in fractures of the extremities; the diagnostic value (sensitivity and specificity) of the 3D-RX-scan in a clinical setting, the therapeutical outcome and its effect on the quality of fracture reduction and fixation and the patient relevant outcomes. For this purpose we prefer a blinded randomized design, offering the most robust way to investigate the effect of the intra-operative use of 3D-imaging. In order to compare both techniques, patients will be randomized during surgery after the definitive adjustments on the basis of 2D-fluoroscopy and before 3D-fluoroscopy. This avoids the phenomenon that the surgeon neglects the 2D-fluoroscopy and relies on the envisioned 3D-images for the reduction and fixation later during the surgical procedure. An additional advantage of this design is that both the diagnostic value as well as the effects on the quality of fracture reduction and fixation can be investigated.

A disadvantage of our study design is that half of the patients receive radiation of the 3D-scan, while they cannot benefit from this 3D-scan. Because of the relatively low radiation dose of the 3D-scan, this disadvantage is considered acceptable.

An alternative, more pragmatic, study design would randomize between two operative strategies: with or without intra-operative 3D-imaging. In this design no patient would receive unbeneficial radiation doses and this set-up will probably be a better reflection of the clinical practice. However, comparing two surgical strategies does not allow the assessment of any missed incongruences when using 2D-fluoroscopy alone. In addition, when the surgeon knows he can employ the 3D-imaging strategy, he might change his attitude towards 2D-fluoroscopy and be less accurate. Hence, more bias will be introduced because of the surgeon's attitude towards 3D-imaging. In addition, 3D-imaging may also detect incongruences that are corrected, but may not have any influence on functional outcomes or long-term development of posttraumatic osteoarthritis. This possible overdiagnosing with 3D-imaging cannot be detected with a pragmatic design.

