**Figure 1 F1:**
[figure not shown]
**Flow chart of the EF3X-trial**.

The randomization will determine whether or not the information of the 3D-scan will be made available to the surgeon. Randomization is performed by an internet randomization module prepared by the AMC Clinical Research Unit. Block randomization is used and randomization will be stratified for the fractured joint (wrist, ankle or calcaneus) and participating centre. Since it is not possible to blind the surgeon, randomization takes place after the surgeon has finished operating based on the information of 2D-fluoroscopy and is ready to close the wound. In this way (s)he cannot anticipate on the likeliness (s)he gets extra information of the 3D-scan. Patients will not be informed about whether or not the 3D-scan was made available to the surgeon.

If the 3D-scan results will not be made available, the surgeon terminates the procedure. If the information of the 3D-scan is available to the surgeon he can act on the findings and, if necessary, surgical corrections can be made. If the surgeon is now satisfied with the operation result conclusive 2D-fluoroscopic images and a conclusive 3D-scan must be performed. The conclusive 3D-scan needs to be evaluated according to the scoring protocol for anatomical reduction. In both randomization groups a CT-scan will be performed postoperatively.

The follow-up visits after hospital discharge will be planned at 6 and 12 weeks and 1, 2 and 5 years postoperatively.

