Before ending the operation, conclusive 2D-fluoroscopic images and a conclusive 3D-RX-scan are being performed. Together with the postoperative CT-scan (reference test) these radiologic images all represent the final operating result. Therefore the diagnostic value of only the conclusive 2D-fluoroscopic images and 3D-RX-scan will be determined. This will be done for the wrist, ankle and calcaneus separately. Hereby the detection of a suboptimal result, as described above, on the 2D-fluoroscopic images and/or 3D-RX-scan will be compared to the postoperative CT-scans.

A cost-effectiveness analysis will be performed to assess the relative benefit from a societal perspective of the use of the 3D-RX-scan in addition to 2D-fluoroscopy.

Our secondary study outcomes are:

> The number and type of corrections made after 2D-fluoroscopy

> The number and type of corrections made after a 3D-scan

> The number of revision operations within 30 days

> The number and type of complications within 30 days

> The length of the hospital stay expressed in days

> The quality of life measured by the SF-36

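### The planned between-group Chi-square tests on intra-operative corrections cannot measure an effect: corrections after 2D precede randomisation, and corrections after 3D are possible in one arm only

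*Protocol article*

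**What the plan says.** Under Primary and secondary endpoints, the protocol article lists two separate secondary outcomes: "The number and type of corrections made after 2D-fluoroscopy" and "The number and type of corrections made after a 3D-scan".

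Data analysis covers both in one sentence: "The number of patients in which corrections were performed intra-operatively after 2D-fluoroscopy or the 3D-RX-scan will be described as percentages". The next sentence reads "Differences between study groups will be analysed by means of a Chi-square test", and the paragraph closes with "For all secondary parameters a p-value < 0.05 will be taken as the threshold for statistical significance". The same test is then extended to revision operations and complications within 30 days.

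The timing is given in two places. Choice for the study design says that "patients will be randomized during surgery after the definitive adjustments on the basis of 2D-fluoroscopy and before 3D-fluoroscopy". Study design (text after Figure 1) says that "randomization takes place after the surgeon has finished operating based on the information of 2D-fluoroscopy and is ready to close the wound". On the blinded arm, the same text says: "If the 3D-scan results will not be made available, the surgeon terminates the procedure". Only in the other arm may the surgeon act on the scan.

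**The concern.** A between-group test in a randomised trial is informative when allocation could have changed the outcome and the outcome could have occurred in either arm. Each of the two correction outcomes fails one of these conditions.

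- **Corrections after 2D** are made before the allocation is known. A significant difference could only be a chance imbalance (or a failure of concealment), yet the plan would report it as a secondary outcome difference.
- **Corrections after 3D** cannot be made in the blinded arm. A significant difference only restates that one group was allowed to act on the scan.

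The second test will almost certainly be significant. The article itself warns, under Choice for the study design and Economic evaluation, that 3D-imaging may lead to corrections of no consequence for the patient. Such corrections would count towards this result exactly as useful ones do, so a reader could take a very small p-value as support for the technique when it carries no information on benefit.

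**Working it through.** **Inputs**

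| Input | Value | Source |
|---|---|---|
| Patients per arm, one fracture type | 122 evaluable; 250/2 = 125 enrolled | Sample size calculation |
| Correction rate after 3D | 11–30% (the Abstract gives 18–30%) | Background |
| Threshold | p < 0.05 | Data analysis |
| Corrections after 3D, blinded arm | 0 by design | Study design |

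**The plan's own figure.** The article gives no figure for the correction outcomes. Its sample size for the primary outcome does reproduce: 17% against 5%, two-sided 0.05, power 0.80, continuity-corrected, gives 122 per group.

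**Corrections after 2D.** Both arms share one true rate, whatever it is. In 200,000 simulated trials with 125 per arm, the uncorrected Chi-square test rejected as follows:

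| True rate in both arms | Rejections at 0.05 |
|---|---|
| 10% | 4.99% |
| 30% | 4.97% |
| 50% | 4.88% |

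This is the nominal error rate and nothing else.

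**Corrections after 3D.** For x corrections among n patients against 0 among n, the 2×2 statistics reduce to

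- uncorrected: χ² = 2n·x / (2n − x)
- continuity-corrected: χ² = 2n·(x − 1)² / [x·(2n − x)]

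With n = 125:

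| x against 0 | χ² uncorrected | p | χ² corrected | p |
|---|---|---|---|---|
| 3 | 250·3/247 = 3.04 | 0.081 | 250·4/(3·247) = 1.35 | 0.245 |
| 4 | 250·4/246 = 4.07 | 0.044 | 250·9/(4·246) = 2.29 | 0.130 |
| 6 | 250·6/244 = 6.15 | 0.013 | 250·25/(6·244) = 4.27 | 0.039 |
| 14 (11%) | 250·14/236 = 14.83 | 0.0001 | 250·169/(14·236) = 12.79 | 0.0003 |

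Significance therefore needs 4 corrections without the continuity correction, or 6 with it. If the true rate is 11%, the binomial probability of reaching those counts is:

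| n per arm | P(X ≥ 4), uncorrected test | P(X ≥ 6), corrected test |
|---|---|---|
| 125 | 0.9997 | 0.995 |
| 122 | 0.9995 | 0.994 |

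At 18% or 30% all of these probabilities exceed 0.99999. With 122 per arm, 13 against 0 (11%) gives p = 0.0002 uncorrected and 0.0006 corrected; 37 against 0 (30%) gives p < 10⁻⁹ either way.

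**All joints together.** Data analysis does not say whether secondary outcomes are tested per joint. With 750/2 = 375 per arm, 4 against 0 still suffices (750·4/746 = 4.02, above 3.84), while the expected count at 11% is 0.11 × 375 ≈ 41.

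**The case against.** The strongest objections are these.

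1. *The comparisons have some use.* A difference in corrections after 2D could point to failed concealment. Any correction after 3D in the blinded arm would show a breach of blinding, which by the article's account rests on turning the screens away. This is fair, and the two comparisons are not wholly without content. But Data analysis presents them as outcome comparisons, on the same footing as revisions and complications, and a breach is shown by a single count, not by a p-value.

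2. *The sentence may mean one pooled variable.* The wording allows it, although the endpoint list separates the two. Pooling does not help: any systematic excess would still come only from corrections that one arm is barred from making.

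3. *Some 2D-based corrections might follow randomisation.* In the scan-available arm, conclusive 2D images are taken after 3D-guided corrections and could prompt more. The article does not say how these would be counted, but they too are impossible in the blinded arm.

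4. *The sections differ on the order of scan and randomisation.* Choice for the study design places randomisation before the 3D-scan, whereas Study design performs the scan and then randomises. Both place it after the 2D-based corrections, so the argument is unaffected.

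5. *The article nowhere calls more corrections a benefit.* This is true; it judges benefit by CT quality and patient outcomes. The risk lies in how a significant p-value will be read, not in a claim the article makes.

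6. *Only secondary outcomes are affected.* This is also true, and it limits the weight of the point.

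**Conclusion.** The concern holds: both tests are wrong as written. The test on corrections after 2D has a null hypothesis that is true by construction, with about a 5% chance of a spurious difference. The test on corrections after 3D compares a positive percentage with a structural zero and is significant with probability 0.9997 uncorrected (0.995 corrected) at an 11% rate with 125 per arm.

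These probabilities assume the lower end of the article's cited range, testing within one fracture type, and adherence to the blinded arm's procedure. Data analysis names a plain Chi-square test, so the uncorrected figure is the closer match. The structural argument needs none of these rates.

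The percentages themselves remain useful descriptively. The primary outcome, the sample size, the functional outcomes, the diagnostic accuracy analysis and the economic evaluation are unaffected. The tests should be changed, but they do not threaten the trial's main conclusion.

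**What to change.** In Data analysis:

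- Remove the between-group test for both correction outcomes. Keep the Chi-square test for revisions and complications within 30 days, and state it there in full, because that sentence now refers back to the one being removed.
- Report corrections after 2D-fluoroscopy, by number and type, as a pre-randomisation characteristic.
- Report corrections after the 3D-scan as a proportion with 95% confidence interval, per joint, in the scan-available arm only. As an illustration, 14/125 = 11.2% with a simple interval of 11.2 ± 1.96·√(0.112·0.888/125) = 11.2 ± 5.5 percentage points, or 5.7% to 16.7%.
- Report any correction after 3D in the blinded arm as a count of protocol deviations.
- For the blinded arm, report the proportion of hidden 3D-scans that the experts rate suboptimal, with 95% confidence interval. This addresses the missed incongruences that the article gives as a reason for its design. It should not be set against the surgeons' correction rate as like with like: the experts judge from images alone, while the surgeon decides in theatre.

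The cost is a few sentences. No new data are needed, since every patient is scanned and the experts already read all intra-operative images. What is lost is two p-values with no interpretation as effects.

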### Economic evaluation

The economic evaluation of intra-operative use of 3D-RX against the use of 2D-fluoroscopy as its best alternative will be performed from a societal perspective as both, a cost-effective and a cost-utility analysis. As the costs of a 3D-RX-system are 1,5 times the costs of a standard C-arm and there is the risk of over diagnosing, an economic evaluation is warranted. This cost-effectiveness analysis is chosen to comply with the clinical endpoint and enables assessment of diagnostic strategies and therapeutic interventions within the field of joint trauma care. The cost-utility analysis is chosen to enable comparisons between the currently proposed optimization of health care (3D versus 2D imaging) on the one hand and new developments and technologies for other diseases and in other areas of medicine on the other hand. The primary outcomes will be the costs per patient with optimal fracture reduction (at 12 weeks post index operation, thus including assessments of re-interventions) and the costs per QALY respectively. The time horizon will be 12 weeks following the index operation. With this length of the follow-up period no discounting of costs will take place.

Incremental cost-effectiveness and cost-utility ratios will be calculated for the extra costs per extra patient with optimal fracture reduction and the extra costs per QALY gained. Univariable and multivariable sensitivity analyses will be applied for unit costs of 3D-scan and country-specific health utility value sets (see below). Bias corrected and accelerated bootstrapping will be done to account for sampling variability. All analyses will be done for each subgroup of patients (with wrist, ankle or calcaneus fracture respectively).

The costs will include the direct medical and non-medical as well as the indirect non-medical costs of care. The direct medical costs include the costs of diagnostics, surgery, in-patient stay, and out-of-hospital care postdischarge (e.g. family practitioner, physiotherapist, rehabilitation care). Also, out-of-pocket expenses of patients will be quantified (over-the-counter medication, private help at home, etc.). The indirect non-medical costs of production loss due to work absenteism will also be calculated. Principally, the friction cost method will be applied to quantify these production losses (in practice though, the length of the friction period at the time of analysis presumably will be longer than the planned follow-up period of patients). Volume data on health care resource use, out-of-pocket expenses and work absenteism will be gathered with case report forms, hospital information systems, and a patient questionnaire, partially based on the Health and Labour questionnaire [26]. Unit costs will derive from the national guideline on costing in health care research [27]. Unit costs will be price-indexed to derive cost estimates for the base year 2011.

Fractures can be quite disabling in daily life. In addition to the already mentioned general (SF-36) and domain-specific (FAOS, PRWE) quality of life questionnaires, the EQ-5D will be applied as a health utility instrument for use in the cost-utility analysis. The health status scoring profiles gathered with the EQ-5D will be transformed into health utilities using available time trade-off based valuation algorithms from the literature. Initially, the Dutch valuations will be used [28]. In a sensitivity analysis the internationally more frequently applied algorithm from the UK will be applied [29].

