**Methods/design:**

In this protocol for an international multicenter randomized clinical trial, adult patients (age > 17 years) with a traumatic intra-articular fracture of the wrist, ankle or calcaneus eligible for surgery will be subjected to additional intra-operative 3D-RX. In half of the patients the surgeon will be blinded to these results, in the other half the surgeon may use the 3D-RX results to further optimize fracture reduction. In both randomization groups a CT-scan will be performed postoperatively. Based on these CT-scans the quality of fracture reduction and fixation will be determined. During the follow-up visits after hospital discharge at 6 and 12 weeks and 1 year postoperatively the patient relevant outcomes will be determined by joint specific, health economic and quality of life questionnaires. In addition a follow up study will be performed to determine the patient relevant outcomes and prevalence of posttraumatic osteoarthritis at 2 and 5 years postoperatively.

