## Methods/design

### Objectives

The objectives of this randomized clinical trial are to:

1. Assess the quality of fracture reduction and fixation based on the postoperative CT-scans of the ankle, calcaneus, or wrist, determined by a standard scoring protocol

2. Assess the patient relevant outcomes

3. Assess the diagnostic value of an intra-operative 3D-RX-scan in a clinical setting

4. Perform a cost-effectiveness analysis to assess whether the use of 2D-fluoroscopy and the 3D-RX-scan eventually results in cost savings or is compensated for by increased health benefits in comparison with the use of 2D-fluoroscopy only

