### Early experience from the ongoing trial

During a period of 15 months 125 patients have been included in one hospital alone. Next to recruitment of patients in the Academic Medical Center (AMC), recruitment will also start in the St. Antonius hospital in Nieuwegein and the University Medical Center Utrecht in the Netherlands. Internationally the University of California San Francisco Medical Center will participate. Patient recruitment in the AMC has gone according to expectations and there are few patients not willing to participate. Due the acute nature of fracture surgery some patients are not able to be counselled and therefore excluded from participation.

For the clinical follow up it appears that 6 weeks postoperative is too early to fill in the selfreported joint-specific questionnaires. Most patients have had 6 weeks of cast immobilisation and have not performed the activities questioned or were advised not to perform some of the activities. For this reason most patients leave some answers blank. Most of the questionnaires filled in after 12 weeks and 1 year postoperatively are filled in correctly and will be used as an endpoint for the clinical outcome.

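### The cost-utility analysis stops at 12 weeks, although its objective looks further ahead and health-economic and quality-of-life questionnaires are planned through 1 year

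*Protocol article*

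**What the plan says.** The Economic evaluation section of the protocol article plans a cost-effectiveness and a cost-utility analysis from a societal perspective. One horizon serves both: "The time horizon will be 12 weeks following the index operation". The two ratios are "the extra costs per extra patient with optimal fracture reduction and the extra costs per QALY gained". The reduction outcome is worded as "costs per patient with optimal fracture reduction (at 12 weeks post index operation, thus including assessments of re-interventions". On uncertainty, the section says that "sensitivity analyses will be applied for unit costs of 3D-scan and country-specific health utility value sets", and adds bootstrapping. It names no other horizon and no extrapolation.

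Other sections look further ahead:

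- Objective 4 (Objectives) asks whether adding the 3D-RX-scan "eventually results in cost savings or is compensated for by increased health benefits".
- Primary and secondary endpoints places the patient-relevant endpoint at 1 year and plans further follow-up at 2 and 5 years.
- The abstract (Methods/design) says that at the visits at 6 weeks, 12 weeks and "1 year postoperatively the patient relevant outcomes will be determined by joint specific, health economic and quality of life questionnaires".
- Early experience from the ongoing trial reports: "Most patients have had 6 weeks of cast immobilisation". It adds that most questionnaires at 12 weeks and 1 year are completed correctly.

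**The concern.** A QALY is utility multiplied by time, so the horizon limits how much benefit can be counted. The rationale given in the Background is that imperfect reduction can lead to osteoarthritis, pain and loss of function. These consequences develop over a longer time than 12 weeks, and most patients spend about half of those 12 weeks in a cast. The extra cost of the scan and of any correction arises at the operation and is counted in full. A health gain that lasts is counted only in part.

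What is at stake is objective 4. The protocol chose the cost-utility analysis so that its result could be set beside innovations in other areas of medicine. A cost per QALY cut off at 12 weeks is hard to use that way, and none of the named sensitivity analyses would show how much depends on the cut-off. The primary clinical comparison is not touched.

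**Working it through.** **Inputs from the protocol article.** Horizon 12 weeks (Economic evaluation); patient-relevant endpoint at 1 year (Primary and secondary endpoints); about 6 weeks in cast for most patients (Early experience); suboptimal result in 17% against 5%, a 12-point difference (Sample size calculation).

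**Inputs assumed.** The utility gain u per patient moved from suboptimal to optimal is not given, so 0.05, 0.10 and 0.20 are used. The gain is taken as constant and lasting.

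**The plan's own figures.** The article gives no derivation for the 12-week horizon, so there is nothing to reproduce. The 12-point effect comes from the sample size, which does reproduce (two-sided α = 0.05, power 0.80):

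- n₀ = [1.96·√(2·0.11·0.89) + 0.842·√(0.17·0.83 + 0.05·0.95)]² / 0.12² ≈ 105.5
- with continuity correction: n = (n₀/4)·[1 + √(1 + 4/(n₀·0.12))]² ≈ 121.6, that is 122 per group, as stated.

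**Step 1: share of the 1-year gain that is captured.** For a constant gain the share is the ratio of the time windows, and u cancels.

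- Gain from surgery onwards: 12/52 = 23.1%, so 76.9% lies outside.
- No gain during 6 weeks in cast (an assumption): (12 − 6)/(52 − 6) = 6/46 = 13.0%, so 87.0% lies outside.

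**Step 2: effect on the cost per QALY.** The ratio is net extra cost divided by QALY gain. At equal net extra cost, the 12-week value divided by the 1-year value is:

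- 52/12 = 4.3 (gain from surgery)
- 46/6 = 7.7 (gain only after the cast)

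**Step 3: absolute scale.** QALY gain per randomised patient = 0.12 × u × T, with the gain from surgery onwards:

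| assumed u | T = 12/52 year | T = 1 year |
|---|---|---|
| 0.05 | 0.0014 | 0.006 |
| 0.10 | 0.0028 | 0.012 |
| 0.20 | 0.0055 | 0.024 |

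**Step 4: relaxing equal cost.** Let the 1-year net extra cost be k times the 12-week value, both positive. The factor in the first case becomes 4.3/k. Later savings (k < 1) widen the gap. Later extra costs (k > 1) narrow it, and the direction reverses once k exceeds 4.3. If the gain is gone by 12 weeks, the QALY gain is the same at both horizons and the factor is 1/k.

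**Step 5: the other ratio.** Cost per extra patient with optimal reduction = net extra cost / 0.12. The denominator contains no T. It is set at the operation or at a re-intervention, so the horizon enters mainly through later costs.

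**The case against.** The strongest defence is that the horizon is openly stated and suits the cost-effectiveness analysis, which the protocol chose to match its clinical endpoint. Reduction is settled at surgery or re-intervention, and 12 weeks largely captures it. That stands, and the point is limited to the cost-utility analysis.

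The second defence is that a lasting gain is assumed. Choice for the study design itself warns that some incongruences corrected after 3D-imaging may not matter for function, and Economic evaluation names a risk of overdiagnosis. The 12-week window also counts offsets such as avoided early revisions, physiotherapy and lost work, while later costs and savings are lost along with later benefit. This stands too. It makes the size and direction conditional, but it does not make 12 weeks suitable for a question about the eventual balance.

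Two stronger readings are tempting. A reader might infer that the evaluation cuts off almost all the benefit and is therefore biased against 3D-RX. The documents do not support this: against the 1-year endpoint, 13% to 23% is captured under a constant gain, and the sign depends on later costs and on whether the gain lasts.

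A reader might also infer that the 12-week reduction outcome cannot be measured, because "In both randomization groups a CT-scan will be performed postoperatively" and Radiation dose counts a single CT-exam. The natural reading, though, is the postoperative CT classification updated for re-interventions. For patients without a re-intervention the CT class simply stands. For re-operated patients the rule is unstated, a detail that an article may leave to the full protocol.

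Finally, the article gives no EQ-5D schedule, so it is an inference that usable 1-year utilities are being collected. The fix has to confirm this.

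**Conclusion.** The point holds for the cost-utility analysis. A 12-week horizon does not fit objective 4 or the 1-year patient-relevant endpoint, and no named sensitivity analysis tests it. If the utility gain is constant and lasting and net extra cost is equal at both horizons, 12 weeks captures 23% of the 1-year QALY gain and the cost per QALY is 4.3 times its 1-year value. If there is also no gain during 6 weeks in cast, the figures are 13% and 7.7. The factors do not depend on the size of the gain, but they do depend on those conditions. They are not an estimate of bias in a known direction. The cost per extra patient with optimal reduction and the primary clinical analysis are largely or wholly unaffected. The change is worth making because the trial already plans questionnaires at 1 year.

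**What to change.** - In Economic evaluation, make 1 year the base-case horizon for costs and QALYs in the cost-utility analysis, using the questionnaires at 6 weeks, 12 weeks and 1 year. Report the 12-week result as a sensitivity analysis. Discounting is still not needed within one year.
- Confirm that the EQ-5D and the resource-use and work items are part of the 1-year questionnaire, and state their schedule.
- Revise the remark that the friction period will presumably exceed patient follow-up. With a 1-year horizon the friction period may become binding.
- Keep the 12-week reduction outcome including re-interventions. Counting re-interventions as costs only would charge an arm for revisions while denying it the corrected result.

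If the items are already collected, the cost is wording plus some analysis work; if not, the 1-year questionnaire must be extended. The downsides are more missing questionnaires at 1 year than at 12 weeks and a resource-use recall interval of 52 − 12 = 40 weeks, over which utility must also be interpolated.
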